**9.3 Epirubicin**

**9.3.1 Availability**

Epirubicin hydrochloride is commercially available as a 2 mg/ml solution for injection in 25 ml and 100 ml vials.

**9.3.2 Preparation**

Please refer to the package insert from the manufacturer for appropriate preparation techniques.

**9.3.3 Storage and Stability**

Intact vials should be stored under refrigeration between 2○ C and 8○ C. Epirubicin is reportedly stable in polypropylene syringes (or the original vial) for at least 14 days at room temperature and 180 days under refrigeration. However, the manufacturer recommends that the solution should be used within 24 hours of penetrating the rubber stopper.

**9.3.4 Administration**

Epirubicin 50 mg / m2 IV bolus will be given on days 1 and 22. Because of significant radiosensitizing toxicities of Epirubicin, the drug will be withheld during radiation treatment. Intravenous administration of Epirubicin should be performed with caution. It is recommended that Epirubicin be administered into the tubing of a freely flowing intravenous infusion (0.9% sodium chloride or 5% glucose solution) over a period of 3 to 15 minutes.

**9.3.5 Toxicity**

Potential toxicities include nausea, vomiting, diarrhea, mucositis, neutropenia, thrombocytopenia, anemia, alopecia, and more rarely cardiotoxicity and second malignancy such as acute leukemia. Necrosis at extravasation and radiation recall can also occur.

**9.4 Dose Modifications and Management of Toxicity**

Toxicity will be graded according to NCI Common Toxicity Criteria.

**9.4.1 Dose Modification for Obese Patients**

All dosing will be calculated according to the patient’s BSA as calculated from actual weight and height. Body surface area will be capped at 2.1 m2.

**9.4.2 Dose Modifications for Chemotherapy**

All dose modifications will be carried forward throughout the chemotherapy and chemoradiotherapy.

If a patient requires a dose reduction of a chemotherapy drug, that dose reduction will continue throughout subsequent chemotherapy and chemoradiotherapy. For example, if a patient requires a 25% reduction during cycle 1 (first cycle of ECF) that patient will receive 75% of the original dose throughout all subsequent cycles of therapy. Similarly, Cisplatin reductions will continue through all cycles. Epirubicin will not be given during cycles with concurrent radiation treatment.

Renal Toxicity.

If, on day 1 of cycles 2-4 the creatinine is greater than 1.5 times the upper limit of normal despite adequate hydration, a calculated creatinine clearance should be performed before that specific cycle is delivered. Based on the calculated creatinine clearance, subsequent dose reductions should be as follows:

If the creatinine clearance ≥ 80 ml/min, no dose reduction is required.

If the creatinine clearance is ≥ 60 and < 80 ml/min the dose of Cisplatinum will be reduced by 50% of the previous dose. The doses of 5-FU and Epirubicin will not change. The doses of Cisplatinum will not be re-escalated in later cycles.

If the creatinine clearance is < 60 ml/min, the patient will go off protocol therapy.

Peripheral Neuropathy.

For grade 0 or 1 peripheral neuropathy, no dose reduction is mandated.

For grade 2 neuropathy, the dose of Cisplatinum will be reduced to 75% of the previous dose. The doses of 5-FU and Epirubicin will not change. The doses of Cisplatinum will not be re-escalated in later cycles.

For grade 3 peripheral neuropathy, the patient should discontinue protocol therapy

Ototoxicity

Any patient developing grade 3 ototoxicity should discontinue protocol therapy.

Hepatic Dysfunction

Patients who develop a bilirubin of > 20 umol/L will have treatment interrupted for one week. Serum bilirubin will be rechecked the following week. If bilirubin is greater than 20 umol/L upon rechecking, treatment will be delayed a second week. If bilirubin remains over 20 umol/L after three weeks, discontinue protocol therapy. Epirubicin will be reduced to 50% of the previous dose for an AST of 2 to 4 times the ULN. Treatment should be held for an AST of > 4 times the ULN. If the AST levels do not resolve to baseline levels within 3 weeks, discontinue protocol therapy.

Cardiotoxicity

Patients developing signs of congestive heart failure should undergo evaluation of ventricular function. If studies demonstrate left ventricular ejection fraction of less than 50%, the patient should discontinue protocol therapy.

Dose Modifications for Stomatitis/Mucositis/Esophagitis/Diarrhea

All patients should be instructed in the appropriate diet and use of loperamide to control diarrhea secondary to chemotherapy, in accordance with the centre standards (for example, loperamide two tablets after each loose bowel movement to a total of 10 tablets per day). If diarrhea persists, or Stomatitis, mucositis or esophagitis occur the following actions should be taken:

*Stomatitis/Mucositis/Esophagitis/Diarrhea*

| CTC Grade at time when next cycle is due to start | Action | Dose of Drug (% previous dose) | | |
| --- | --- | --- | --- | --- |
|  |  | 5-FU | Epirubicin | Cisplatinum |
| 0 | Continue therapy | 100% | 100% | 100% |
| 1 | Continue therapy | 100% | 100% | 100% |
| 2 | Hold therapy for at least one week. Resume when toxicity ≤ 1 | 75% | 100% | 100% |
| 3 | Hold therapy for at least one week. Resume when toxicity ≤ 1 | 75% | 75% | 100% |
| 4 | Hold therapy for at least one week. Resume when toxicity ≤ 1 | 75% | 75% | 100% |

Doses of chemotherapy that have been reduced will not be re-escalated.

Dose Modification for Palmar-plantar erythrodysethesias

*Palmar-plantar erythrodysethesias (Hand-Foot-syndrome)*

| CTC Grade at time when next cycle is due to start | Action | Dose of Drug (% previous dose) | | |
| --- | --- | --- | --- | --- |
|  |  | 5-FU | Epirubicin (if applicable) | Cisplatinum |
| 0 | Continue therapy | 100% | 100% | 100% |
| 1 | Continue therapy and start pyridoxine 50 mg po TID | 100% | 100% | 100% |
| 2 | Hold therapy for at least one week. Resume when toxicity ≤ 1 Start pyridoxine 50 mg po TID | 75% | 100% | 100% |
| 3 | Hold therapy for at least one week. Resume when toxicity ≤ 1 Start pyridoxine 50 mg po TID | 75% | 100% | 100% |

Patients who do not recover to ≤ grade 1 within 3 weeks will discontinue protocol therapy.

Hematologic Toxicity

Patients whose platelet and/or neutrophil counts are low will have their therapy delayed (with weekly bloodwork) until adequate counts are achieved. The dose of chemotherapy used when therapy is resumed is adjusted as indicated in the following table (applies to all agents in a multi-agent regimen).

A new dose of chemotherapy should not be initiated (including the next seven days of a continuous 5-FU infusion in the postoperative arm) unless the absolute neutrophil count (ANC) is ≥ 1500/mm3 and the platelet count is ≥ 100,000/mm3.

Patients who experience neutropenia and do not recover to ANC ≥ 1500/mm3 within 3 weeks will discontinue protocol therapy.

Patients who experience thrombocytopenia and do not recover to platelet count ≥ 100,000/mm3 within 3 weeks will discontinue protocol therapy.

Dose to be given at next cycle (as percentage of the dose calculated based on body surface area), tabulated by worst myelosuppression experienced in previous cycle

| \| Dose to be given at next cycle (as percentage of the dose calculated based on body surface area), tabulated by *worst* myelosuppression experienced in *previous* cycle \| \| --- \| |
| --- | --- |
| \| Platelet Count (10^9^/L) \| Neutrophil or Granulocyte Count (10^9^/L) \| \| \| \| \| --- \| --- \| --- \| --- \| --- \| \|  \| > or = 1.5 \| 1 - 1.49 \| 0.5 - 0.99 \| < 0.5 \| \| > or = 100 \| 100% \| 100% \| 75% \| 50% \| \| 50-99 \| 100% \| 100% \| 75% \| 50% \| \| 25-49 \| 75% \| 75% \| 75% \| 50% \| \| < 25 \| 50% \| 50% \| 50% \| 50% \| |
| \|  \| \| --- \| |

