**5.0 Research Design and Methods**

**5.1 Eligibility Criteria**

5.1.1 Histologically documented squamous cell carcinoma or adenocarcinoma of the thoracic esophagus (> 20 cm from the incisors) or gastroesophageal junction are included. Cancers of the cervical esophagus (< 20 cm are excluded).

5.1.2 No distant metastases (M0).

5.1.3 Patients will be stratified by stage (clinical N0 versus clinical N1), and surgeon (RI versus RM versus DF)

5.1.4 Patients with tumours within 3 cm distal spread into gastric cardia as detected by esophagogastroscopy. Tumours that have > 3 cm of spread into cardia of the stomach are considered gastric cancers and are ineligible.

5.1.5 Patients with biopsy (by endoscopic ultrasound, laparoscopy, or laparotomy) proven metastatic supraclavicular nodes are ineligible.

5.1.6 Patients with biopsy proven metastatic celiac nodes are ineligible. Resectable mediastinal nodes are eligible.

5.1.7 No prior chemotherapy for this malignancy.

5.1.8 No prior radiotherapy that would overlap the field(s) treated in this study.

5.1.9 Patients with other malignancies are eligible only if > 5 years without evidence of disease or completely resected or treated non-melanoma skin cancer.

5.1.10 Age > 18 years and able to tolerate tri-modality therapy at the discretion of the treating thoracic surgeon, medical and radiation oncologists. Tumours must be resectable after assessment by the thoracic surgeon.

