**5.1.11 Required Laboratory Data:**

Granulocytes > 1.5 x 103 / L

Thrombocytes > 100 x 103 / L

AST, ALT, ALP < 2 times upper limit of normal

Creatinine clearance > 50 ml / min*

x Measurement or calculation based on gender from serum creatinine, age, and body weight (kg) according to the formula below:

For men: (140 - age) x (body weight in kg)

(72 x serum creatinine)

For women: 0.85 x (creatinine clearance)

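### The renal dosing rule checks creatinine clearance only after serum creatinine passes 1.5 x ULN, so an older or lighter patient can fall below the entry limit of 50 mL/min with no change to cisplatin ordered

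*Protocol*

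**What the plan says.** Protocol 5.1.11 lists as an entry requirement "Creatinine clearance > 50 ml / min". The value may come from "Measurement or calculation based on gender from serum creatinine, age, and body weight (kg) according to the formula below". The formula for men is (140 - age) x weight in kg, divided by 72 x serum creatinine; for women the result is multiplied by 0.85.

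The renal part of 9.4.2 works in two steps. First, on day 1 of cycles 2 to 4, if creatinine is "greater than 1.5 times the upper limit of normal despite adequate hydration, a calculated creatinine clearance should be performed" before that cycle is given. Second, the calculated value sets the dose:

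- 80 mL/min or more: no reduction.
- 60 to below 80: "the dose of Cisplatinum will be reduced by 50% of the previous dose".
- Below 60: "If the creatinine clearance is < 60 ml/min, the patient will go off protocol therapy".

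The second step applies only to patients who meet the first. No other part of the protocol requires clearance to be rechecked during treatment; the weekly bloodwork in 9.4.2 concerns low platelet and neutrophil counts.

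**The concern.** Clearance depends on age, weight and sex as well as on creatinine. A trigger set on creatinine alone, as a multiple of a laboratory limit, therefore corresponds to very different clearances in different patients. In an older or lighter patient, clearance may already be well under both 50 and 60 when creatinine is still short of the trigger. The protocol's safeguard would then not come into play for the patients with least renal reserve.

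Section 9.1.4 lists renal toxicity among the common effects of cisplatin. What is at stake is the safety of further full-dose cycles at a clearance that would have barred entry.

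**Working it through.** The protocol states no figure on this point to reproduce, so the check applies its own formula at its own trigger.

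**Inputs from the protocol.** Formula and entry limit from 5.1.11; trigger and bands from 9.4.2; cisplatin doses from 9.0 and 9.1.3.

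**Assumptions not in the protocol.** Creatinine in mg/dL (the constant 72 implies this unit); ULN 1.0, 1.2 or 1.4, so the trigger is 1.5, 1.8 or 2.1; clearance calculated rather than measured at entry; the 5.1.11 formula also used in 9.4.2. The example patients are illustrative.

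**Step 1: clearance as a function of creatinine.** For a given patient, clearance = k / creatinine, where k = (140 - age) x kg / 72, times 0.85 for women.

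- Man, 75 y, 60 kg: 65 x 60 / 72 = 54.17
- Woman, 65 y, 65 kg: 0.85 x 75 x 65 / 72 = 57.55
- Man, 65 y, 70 kg: 75 x 70 / 72 = 72.92
- Man, 65 y, 75 kg: 75 x 75 / 72 = 78.13
- Man, 50 y, 90 kg: 90 x 90 / 72 = 112.5

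**Step 2: where each patient crosses 60 and 50, and the clearance at the trigger.**

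| Patient | Creatinine at clearance 60 | Creatinine at clearance 50 | Clearance at trigger, ULN 1.0 / 1.2 / 1.4 |
| --- | --- | --- | --- |
| Man 75 y, 60 kg | 0.90 | 1.08 | 36.1 / 30.1 / 25.8 |
| Woman 65 y, 65 kg | 0.96 | 1.15 | 38.4 / 32.0 / 27.4 |
| Man 65 y, 70 kg | 1.22 | 1.46 | 48.6 / 40.5 / 34.7 |
| Man 65 y, 75 kg | 1.30 | 1.56 | 52.1 / 43.4 / 37.2 |
| Man 50 y, 90 kg | 1.88 | 2.25 | 75.0 / 62.5 / 53.6 |

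**Step 3: read the cases.**

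- The first man is eligible at creatinine 1.0 (54.2). At 1.2 he has 45.1, untriggered at every ULN assumed.
- The woman is eligible at 1.0 (57.6) and at 1.2 has 48.0, also untriggered throughout.
- The third patient crosses both limits. At 0.9 he has 81.0; at 1.5 he has 48.6, a fall of 40% (1 - 0.9/1.5). Creatinine of 1.5 does not exceed any of the three triggers.
- The fourth crosses 60 untriggered at every ULN assumed, but crosses 50 untriggered only at ULN 1.2 or 1.4.
- The fifth never falls below 50 untriggered, and falls below 60 untriggered only at ULN 1.4.

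**Step 4: general condition for men.** Clearance at the trigger is below 50 if (140 - age) x kg < 72 x 1.5 x 50 x ULN = 5400 x ULN. For ULN 1.0 / 1.2 / 1.4 this means weights below:

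- age 50: 60 / 72 / 84 kg
- age 65: 72 / 86 / 101 kg
- age 75: 83 / 100 / 116 kg

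**Step 5: exposure.** Control arm: 4 x 25 = 100 mg/m2 per cycle, two cycles, so 100 of 200 mg/m2 remains after cycle 1. Experimental arm: 60 mg/m2 per cycle, four cycles, so 180 of 240 mg/m2 remains. Resected pT1N0 and pT2N0 patients in the experimental arm are not offered adjuvant therapy (section 10.0), so this does not apply to them.

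**The case against.** The strongest reply is that the rule is explicit and usable. The trigger applies only after adequate hydration, so it screens out transient rises, and each triggered patient has one defined action. Section 9.1.3 calls for prehydration and renal-protective measures, 15.0 tells the oncologist to act in the patient's best interest, and 16.0 makes study physicians responsible for safety. Nobody is compelled to give full-dose cisplatin to a patient with failing kidneys. This stands as far as it goes, but general clauses leave the decision to individual judgement; they do not supply the check that the specific rule omits.

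A reader might also infer that on-treatment limits must equal entry limits. The document does not support that. Entry needs AST below 2 x ULN, yet 9.4.2 answers an AST of 2 to 4 x ULN only by halving epirubicin and holds treatment only above 4 x ULN. The blood-count rule, under which no new dose starts "unless the absolute neutrophil count (ANC) is ≥ 1500/mm3 and the platelet count is ≥ 100,000/mm3", shows that a direct check before each dose is workable here. It does not show that the two sets of limits must agree.

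A second tempting reading is that a stop limit of 60 contradicts an entry limit of 50, so that entrants at 51 to 59 are removed at cycle 2. That does not follow either. Clearance is not calculated unless creatinine passes the trigger, and entry also requires a patient "able to tolerate tri-modality therapy at the discretion of the treating thoracic surgeon, medical and radiation oncologists". An entrant in that range whose creatinine already exceeds the trigger is conceivable, but nothing in the protocol shows that such patients would be enrolled.

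Finally, the ULN and the example patients are assumed. That is correct. The result for the first three patients holds across the whole assumed ULN range, but their share of the trial population is unknown.

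**Conclusion.** The point holds as a gap in a safety rule. As written, 9.4.2 can leave an older or lighter patient below the entry limit of 50 mL/min, and below its own stop limit of 60, with no clearance calculated and no change to full-dose cisplatin ordered. In the examples the clearance at the trigger is as low as 26 to 36 mL/min (man of 75, 60 kg), while a man of 50 weighing 90 kg is not missed at the limit of 50.

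This rests on creatinine in mg/dL, a ULN of 1.0 to 1.4 and clearance calculated by the 5.1.11 formula. The protocol gives no distribution of age, weight or clearance, so frequency cannot be estimated and no claim is made that many patients would be affected. It is a dosing and safety matter only: sample size, alpha and the intention-to-treat analysis do not change.

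**What to change.** In 9.4.2, require clearance to be calculated by the 5.1.11 formula, from day-1 creatinine, age and current weight, before every cisplatin cycle from cycle 2, whatever the serum creatinine. Give no further cisplatin if the result is not above 50 mL/min, and state whether 5-FU and radiation then continue. Leave the entry limit and the existing bands for triggered patients as they are.

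This does not remove every difference by trigger status: an untriggered patient between 50 and 60 would still receive full dose, while a triggered one would leave protocol therapy. Whether to apply the 60 to 79 and below-60 bands to all patients is a clinical choice for the trial's oncologists.

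The cost is a wording amendment and one arithmetic step. The rule already relies on day-1 creatinine and age is on record, so a current weight is the only possible addition. The downside is that some older or lighter patients would stop cisplatin earlier, occasionally on a small rise: the man of 75 weighing 60 kg reaches 50 at creatinine 1.08, against 1.0 at entry. Parts of section 17 are written in the past tense; if treatment is already complete, the point serves only for reading the toxicity comparison.

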**Arm II: Postoperative Chemotherapy (Experimental Arm) QUINTETT-ADJ**

Treatment should begin between 8 to 12 weeks following surgery.

The chemotherapy treatment is as follows:

Chemotherapy alone for 2 cycles – One cycle consists of Epirubicin 50 mg/ m2 and Cisplatin 60 mg/m2 day 1, and 5-Fluorouracil (5FU) by continuous venous infusion at 200 mg/m2 for 21 days.

Chemotherapy (concurrent with radiation) immediately afterwards for 2 additional cycles – One cycle consists of Cisplatin 60 mg/m2 day 1, and 5-Fluorouracil (5FU) by continuous venous infusion at 200 mg/m2 for 21 days. Concurrent radiation is to start on the same day as cisplatin is administered if possible, but in all cases within 3 days before or after that date.

Details regarding the chemotherapeutic agents:

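### Section 9.4.2 contradicts itself on the dose after a haematologic reduction: half or full dose could follow in the experimental arm's radiation cycles

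*Protocol*

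**What the plan says.** All of the conflicting text is in Protocol section 9.4.2, Dose Modifications for Chemotherapy.

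- **General rule.** The section opens: "All dose modifications will be carried forward throughout the chemotherapy and chemoradiotherapy". Its example is a patient who needs a 25% reduction in cycle 1, and it concludes "that patient will receive 75% of the original dose throughout all subsequent cycles of therapy".
- **Stomatitis/mucositis/esophagitis/diarrhea and hand-foot tables.** Both are headed "Dose of Drug (% previous dose)". Directly under the first of them stands "Doses of chemotherapy that have been reduced will not be re-escalated".
- **Haematologic table.** Its lead-in says that patients with low counts are delayed until counts are adequate, and that the dose on resumption follows the table, which "applies to all agents in a multi-agent regimen". The caption defines the dose for the next cycle "as percentage of the dose calculated based on body surface area), tabulated by worst myelosuppression experienced in previous cycle". Four of the 16 cells read 100%.

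On the schedule, section 9.0 gives Arm I two cycles, both with radiation. Arm II has two cycles of chemotherapy alone and then "Chemotherapy (concurrent with radiation) immediately afterwards for 2 additional cycles". Section 10.0 confirms that radiation in Arm II starts with cycle 3.

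**The concern.** The general rule looks back over the whole course: once a dose is cut, the cut stays. The haematologic table looks back one cycle only and refers to the full calculated dose. Taken as written, the table returns a patient to 100% when counts improve on a reduced dose, which the general rule does not allow.

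The first cycle at which this can happen is cycle 3 of Arm II, when radiation starts. Two prescribers following the same section could therefore give doses that differ two-fold at that point. This bears on patient safety. It also bears on how uniformly the experimental treatment is delivered, in a trial that compares toxicity between arms as a secondary objective (section 3.2.1).

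**Working it through.** **Inputs**

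- Carry-forward rule and example: opening of section 9.4.2.
- Haematologic table, section 9.4.2: four platelet bands by four neutrophil bands, 16 cells. Four cells read 100%, five read 75% and seven read 50%.
- Counts needed to start a dose, section 9.4.2: neutrophils at least 1500/mm³ and platelets at least 100,000/mm³.
- Arm II cycles 3 and 4, sections 9.0 and 9.2.4: cisplatin 60 mg/m² on day 1 and 5-FU 200 mg/m²/day for 21 days. Epirubicin is not given with radiation.
- Arm I, section 9.0: two cycles.

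**Step 1. The protocol's own example.** 100% − 25% = 75% of the original dose, as stated. At a first reduction, the original dose, the previous dose and the calculated dose are the same quantity, so the rules agree. They can part only when a later cycle's counts select the dose again.

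**Step 2. A path on which they part (Arm II).**

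| Event | Haematologic table | Carry-forward rule |
| --- | --- | --- |
| Cycle 1 worst neutrophils < 0.5 → cycle 2 dose | 50% | 50% |
| Cycle 2 worst neutrophils 1.0–1.49, platelets ≥ 50 → cycle 3 dose | 100% | 50% |

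Ratio at cycle 3: 100% / 50% = 2.

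**Step 3. In planned doses.**

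- Cisplatin at cycle 3: 60 × 1.00 = 60 versus 60 × 0.50 = 30 mg/m².
- 5-FU at cycle 3: 200 × 1.00 = 200 versus 200 × 0.50 = 100 mg/m²/day.
- If counts call for no further cut, over cycles 3 and 4: cisplatin 2 × 60 = 120 versus 2 × 30 = 60 mg/m²; 5-FU 200 × 42 = 8400 versus 100 × 42 = 4200 mg/m².

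**Step 4. How much of the table is affected.** Over two consecutive cycles there are 16 × 16 = 256 pairs of cells. The table exceeds carry-forward when the second cell is higher than the first:

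- 50% then 100%: 7 × 4 = 28 pairs
- 75% then 100%: 5 × 4 = 20 pairs
- 50% then 75%: 7 × 5 = 35 pairs
- Total: 28 + 20 + 35 = 83 of 256

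Suppose instead that the lead-in confines the table to patients whose counts were low. The cell with neutrophils ≥ 1.5 and platelets ≥ 100 then drops out as a second cell, leaving three 100% cells. The counts become 7 × 3 = 21, 5 × 3 = 15 and 35, in total 71 of 16 × 15 = 240. The half-versus-full case survives. These are counts of table cells, not probabilities for patients.

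**Step 5. Arm I.** A reduction for cycle 1 counts takes effect at cycle 2, which is the last planned cycle. There is no third cycle at which to undo it.

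**The case against.** The strongest reply is that the texts can be read together. The table sits inside a section whose first sentence covers all modifications, and nothing exempts it. On that reading the table sets any new reduction and the general rule preserves an old one. The reading is reasonable, but the protocol does not state it. The caption defines the next dose outright, and a reader could equally take the specific table as governing.

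A second reply is that the lead-in ties the table to patients delayed for low counts. This has force for a patient whose worst cycle 2 counts meet both starting thresholds: on that reading the table is never consulted and carry-forward stands. It does not remove the conflict. Neutrophils of 1.0–1.49 or platelets of 50–99 are below the starting thresholds. If they persist when cycle 3 is due, treatment is delayed, and with the other count in its top two bands the cell on resumption still reads 100%.

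Three stronger readings might be inferred and are not supported:

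- **The no-re-escalation sentence settles the matter.** It stands under the stomatitis/diarrhea table and may be limited to it. The other such sentences in 9.4.2 concern cisplatin after renal toxicity or neuropathy. The contradiction rests on the general rule alone.
- **The different bases conflict numerically after two 25% cuts** (0.75 × 0.75 = 56% against 75%). The protocol's example covers a single reduction and does not say what follows a second toxicity, so this is not a contradiction with it.
- **Every agent is affected.** In cycles 3 and 4 only cisplatin and 5-FU are given.

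**Conclusion.** The contradiction is real and lies within one section. After a haematologic reduction in Arm II, the general rule and the haematologic table can prescribe cycle 3 doses that differ by up to a factor of two for cisplatin and 5-FU, and no sentence gives precedence. The two-fold figure assumes a worst neutrophil count below 0.5 (or platelets below 25) in cycle 1, with worst counts in cycle 2 of at least 1.0 and platelets of at least 50. If the table applies only after a delay, it also assumes that low counts persist when cycle 3 is due.

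The number of patients affected is unknown. The protocol gives no rate of reduction followed by recovery, and section 10.0 offers no adjuvant therapy to patients resected at pT1N0 or pT2N0. A reader might infer that the ambiguity biases the FACT-E comparison, because this reversal can arise only in Arm II. The protocol gives neither a size nor a direction for such an effect, so that inference is not made here. The sample size is not touched. No view is taken on which dose is right.

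**What to change.** Reconcile the parts of section 9.4.2: the opening rule, the two tables based on the previous dose, and the haematologic table. State one reference dose for all of them, and state whether the haematologic table is subject to the carry-forward rule. The choice of rule is the sponsor's.

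Then check that the order sets named in section 9.0 for the two arms apply the same wording. They are not shown in the protocol, so whether they need changing is unknown.

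The cost is a wording amendment, plus an edit to the order sets if they differ. The randomization, sample size and data collection do not change.
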